Given these findings, the key question is whether the type of nature-based activity creates a significant difference in its effectiveness on the cognitive and mental health of older adults, and if so, which type of intervention is more effective and what is the nature of its impact? This issue represents a significant research gap, and its investigation could optimize nature therapy programs for older adults to aid in the design of cognitive decline prevention programs. This study aims to address it by primarily comparing two specific structured activities, walking with meaningful conversations and meditation in nature, with a focus on two key psychological outcomes: mental vitality, defined as the subjective experience of energy and aliveness [13], and cognitive empowerment, understood as the perceived capacity to adapt to and manage one’s cognitive engagement [14]. The results will subsequently be compared with a control group.

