### Sample size

The required sample size was calculated using G* Power software, based on the method described by Kazazi et al. [13]. Among the study objectives, the one requiring the largest sample was selected as the basis for estimation, specifically the evaluation of the intervention’s effect on cognitive empowerment in older adults. According to prior data, the mean (±standard deviation) of the mental status examination scores after the intervention was 28.3 ± 1.8 in the intervention group and 27.5 ± 2.1 in the control group. Using these values, the calculated effect size was 0.41. With a statistical power of 95% and an alpha level of 0.05, and assuming two repeated measurements after the intervention, the minimum required sample size was determined to be 58 participants. To account for a possible 20% attrition rate and a design effect of 1.6 due to cluster sampling, the final adjusted sample size was increased to 111 participants, resulting in 37 individuals per group.

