### Outcomes

#### Primary outcome

The primary outcome is the change in Cognitive Empowerment score from baseline to the post-intervention assessment at week 8. To measure this variable, the Ability to Recognize Cognitive Changes questionnaire will be used. This questionnaire was designed and psychometrically evaluated by Tarighat et al. [14]. The questionnaire consisted of 25 questions that assessed older adults’ ability to recognize their own cognitive changes across 8 dimensions on a 3-point scale: physical strength (5 questions), self-esteem (5 questions), spirituality (2 questions), commitment (2 questions), role performance (4 questions), situation recognition (2 questions), self-management (3 questions), and self-assessment (2 questions). The total score ranged from 25 to 75. A score of 0 to 25 indicates that older adults’ ability to recognize cognitive changes is at an unfavorable level, 25 to 50 at a relatively favorable level, and a score above 50 at a favorable level. The questionnaire’s reliability and validity have been established, demonstrating satisfactory content and construct validity alongside a Cronbach’s alpha of 0.70.

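### The effect size of 0.41 behind the sample size comes from a mental status examination, not the primary questionnaire, so the stated 95% power is not established for the primary outcome

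*Protocol article*

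**What the plan says.** The Sample size section says the objective needing the largest sample was chosen as the basis, "specifically the evaluation of the intervention’s effect on cognitive empowerment in older adults". The only data it gives are prior results in which "the mean (±standard deviation) of the mental status examination scores after the intervention was 28.3 ± 1.8 in the intervention group and 27.5 ± 2.1" (controls second). It continues: "Using these values, the calculated effect size was 0.41". The power and alpha are given as "With a statistical power of 95% and an alpha level of 0.05". The repeated-measures setting is "assuming two repeated measurements after the intervention". The result is a minimum of 58, raised to 111 (37 per group) for 20% attrition and a design effect of 1.6.

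The Primary outcome section reads: "The primary outcome is the change in Cognitive Empowerment score from baseline to the post-intervention assessment at week 8". The instrument is the Ability to Recognize Cognitive Changes questionnaire, with 25 items on a 3-point scale: "The total score ranged from 25 to 75". The Introduction defines the construct as "cognitive empowerment, understood as the perceived capacity to adapt to and manage one’s cognitive engagement".

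Statistical methods sets a Bonferroni-corrected alpha of 0.0167 for each of the three pairwise comparisons on the primary outcome.

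**The concern.** The calculation is presented as being about cognitive empowerment, but no cognitive empowerment figure enters it. The source differs from the endpoint in two respects that matter.

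- **Instrument and construct.** The source is an examination of mental status. The endpoint is self-reported perceived capacity on another scale.
- **Quantity.** The source is a score after the intervention. The endpoint is a change from baseline.

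No mental status examination appears among the outcomes. The only cognitive test in the trial is the Mini-Cog, a screening tool scored 0 to 5, so the values 28.3 and 27.5 cannot come from it.

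What is at stake is how the primary result will be read. Someone who meets a non-significant result and looks up the sample size section would credit the trial with 95% power for cognitive empowerment, when the calculation shown was made for something else. The article gives no SD, expected difference or important difference for the questionnaire, so the effect the trial is designed to find cannot be stated in questionnaire points.

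**Working it through.** **1. Where 0.41 comes from.** Inputs from the Sample size section: means 28.3 and 27.5, SDs 1.8 and 2.1.

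- Pooled SD = √((1.8² + 2.1²)/2) = √3.825 = 1.956.
- d = (28.3 − 27.5)/1.956 = 0.8/1.956 = 0.409.

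This reproduces the stated 0.41. It is a Cohen's d derived wholly from the mental status examination and carries no information about the questionnaire.

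**2. Source and endpoint side by side.**

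| | Source of 0.41 | Primary endpoint |
|---|---|---|
| Measure | Mental status examination | Ability to Recognize Cognitive Changes questionnaire |
| Quantity | Post-intervention score | Change, baseline to week 8 |
| Mean and SD | 28.3 ± 1.8 vs 27.5 ± 2.1 | None given (score range 25 to 75) |
| Used in this trial | No | Yes |

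No sentence links the two columns.

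**3. What the design can detect without a borrowed effect.** Inputs: 37 per arm (Sample size), two-sided alpha 0.05/3 = 0.0167 (Statistical methods), and 80% power as a conventional reference. The method is noncentral-t power for a comparison of two means, solved for d.

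- 37 per arm: d = 0.768, about 0.77 SD.
- After 20% attrition, 37 × 0.8 = 29.6, about 30 per arm: d = 0.86 SD.

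The unit is the SD of whatever is analysed, here the change score. No design effect is applied, and no gain from baseline adjustment or repeated measures.

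**4. Why one SD is not enough to convert to points.** If the SD is the same at both times and r is the baseline to week-8 correlation, SD of change = SD × √(2(1 − r)). Taking 0.768 change-score SDs and assuming r between 0.2 and 0.7:

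- r = 0.2: 0.768 × √1.6 = 0.768 × 1.265 = 0.97 cross-sectional SD.
- r = 0.5: 0.768 × √1.0 = 0.77.
- r = 0.7: 0.768 × √0.6 = 0.768 × 0.775 = 0.59.

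The article gives neither the SD nor r for the questionnaire, so no figure in points follows from it.

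**5. Does change instead of post-score help or hurt?** Taking the examination figures as an example (difference 0.8, SD 1.956 at both times, 37 per arm, alpha 0.05), power is 28% at r = 0.2, 41% at r = 0.5 and 61% at r = 0.7. The direction depends on r, so the mismatch in quantity is not in itself a loss of power.

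**The case against.** The best defence is that power depends on the standardized effect, and 0.41 has no units. Sizing a trial from a related measure is common when the chosen instrument has no usable data. If d = 0.41 also held for change on the questionnaire, the change of instrument would not by itself invalidate the power figure. This stands as far as it goes: a transfer of this kind is legitimate when it is stated and argued. Here it is neither.

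The defence also disposes of some stronger readings.

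- **Floor and SD.** A reader might infer that the plan expects means near 28 and an SD near 2 on a 25 to 75 scale, which would look implausible. The article does not say this. It carries over a standardized effect, not raw points or an SD.
- **Collapse of power.** A reader might place a 0.8-point difference on the wider scale and conclude that power is very low. That rests on the same misreading and on an SD the article does not supply.
- **Largest-sample claim.** A reader might conclude that it is false. The article shows no comparison across objectives, so the claim is unsupported in the text. A condensed article may omit such a comparison, and nothing shows that it was not made.
- **Uninterpretable null result.** What a null result excludes is set by its confidence interval, not by planning inputs. The Discussion already warns that the sample size may limit power.

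Whether 58 follows from d = 0.41, and why 0.05 was used in sizing when 0.0167 is planned for the analysis, are separate questions. Resolving either would leave the instrument mismatch in place.

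**Conclusion.** The point holds in a limited form. The calculation is labelled as one for cognitive empowerment, but its effect size belongs wholly to an instrument the trial does not use as an outcome, and the assumption that it carries over is neither stated nor supported. The 95% power is therefore not established for the primary outcome. It is not shown that the true power for that outcome has any particular lower value because of the mismatch.

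The size can be given only in SD units: the 0.77 and 0.86 SD found above, against a planned effect of 0.41. Part of that gap reflects the smaller alpha and the simple two-arm comparison, not the borrowed instrument. The figures assume equal arms, equal variances and independent observations. The mismatch itself rests on no assumption, only on reading Sample size against Primary outcome.

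**What to change.** In the Sample size section:

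1. Keep the enrolment target of 111.
2. Remove the statement that the mental status examination figures give 95% power for cognitive empowerment. Label d = 0.41 as an assumption taken from another instrument, and add a reason for the transfer if there is one.
3. State the difference detectable at alpha 0.0167 in SD units of the analysed outcome, with and without the 20% attrition, and say that design effect and any gain from baseline or repeated measures are not included.
4. Convert to points on the 25 to 75 scale only with a stated SD and a stated baseline to week-8 correlation. One route is a pooled SD, taken blind to arm from the planned baseline questionnaires, with a range of correlations. A baseline SD alone does not give the SD of change.
5. Say that the primary result will be interpreted by its confidence interval.

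The cost is one rewritten paragraph and one blinded SD calculation, with no extra participants. Trial status says recruitment has not started, so the text can be changed before any outcome is known. The downside is that the printed 95% power gives way to a less favourable detectable difference.

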### Statistical methods

To assess the homogeneous distribution of confounding variables across the three groups before the intervention, the chi-square test was used for categorical variables, and one-way ANOVA was applied for continuous variables. All analyses will follow the intention-to-treat principle. Missing data (up to 14%) will be imputed using regression methods.

The primary analysis will test the superiority of the interventions on the primary outcome: change in cognitive empowerment score at week 8. To account for multiple comparisons, the significance level for the three pre-planned between-group comparisons (walking vs. control, meditation vs. control, walking vs. meditation) will be adjusted using the Bonferroni correction, resulting in a corrected alpha of 0.0167.

Changes in outcomes over time, between groups, and their interaction will be analyzed using the generalized estimating equation (GEE) model. Baseline individual and clinical variables showing significant between-group differences (e.g., age, marital status, physical activity) will be included as covariates to control for potential confounding. Analyses for secondary outcomes will be considered exploratory.

All analyses will be conducted using Stata version 17, with a two-tailed alpha level of 5% for tests not covered by the primary correction. Graphs will be generated using GraphPad Prism version 8.

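### The 95% power claim does not hold for the primary comparisons: 58 does not follow from d = 0.41 at ordinary correlations, and the sizing alpha (0.05) is not the testing alpha (0.0167)

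*Protocol article*

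**What the plan says.** The Sample size section takes post-intervention mental status examination scores from prior data, "28.3 ± 1.8 in the intervention group and 27.5 ± 2.1 in the control group", and reports that "Using these values, the calculated effect size was 0.41". It then sets the error rates and design: "With a statistical power of 95% and an alpha level of 0.05, and assuming two repeated measurements after the intervention". The result is that "the minimum required sample size was determined to be 58 participants". Allowances of 20% for attrition and 1.6 for cluster sampling raise this to 111, or 37 in each of three arms. The section names no test family, no correlation between measurements and no number of groups.

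Elsewhere the protocol fixes a different primary test. The Primary outcome section defines the endpoint as the change in cognitive empowerment from baseline to week 8, on an instrument scored 25 to 75: "To measure this variable, the Ability to Recognize Cognitive Changes questionnaire will be used". Statistical methods plans three pairwise comparisons with a Bonferroni adjustment, "resulting in a corrected alpha of 0.0167".

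**The concern.** The calculation and the primary analysis differ in three respects: the alpha (0.05 against 0.0167), the time points (two post-intervention measurements against week 8 alone), and the instrument (a mental status examination against the cognitive empowerment questionnaire). In addition, 58 is very small for a standardised difference of about 0.4 at 95% power.

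If the power is far below 95%, a true effect of the assumed size could easily be missed. A reader who trusts the 95% would then take a non-significant result as good evidence of no effect.

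**Working it through.** **Inputs from the protocol.** Means 28.3 and 27.5; SDs 1.8 and 2.1; power 95%; sizing alpha 0.05; two post-intervention measurements; base size 58; attrition 20%; design effect 1.6; 37 per arm; testing alpha 0.0167. Tests are taken as two-sided, as Statistical methods states for its 5% tests. The correlation r between baseline and week 8 is not given, so it is varied.

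**1. The plan's own figures.** The pooled SD is √((1.8² + 2.1²)/2) = 1.956, and d = 0.8/1.956 = 0.409. The 0.41 reproduces, as Cohen's d. The inflation also reproduces: 58 × 1.2 × 1.6 = 111.36, or 111.

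**2. Does d = 0.41 lead to 58 (alpha 0.05, 95% power)?**
- Between-groups repeated-measures test, two groups, m = 2 measurements. The noncentrality is λ = f²Nm/(1 + (m − 1)ρ), with f = d/2 = 0.205. The total N is 158 at ρ = 0 and 234 at ρ = 0.5. At N = 58 and ρ = 0.5, power is 43%.
- Group-by-time interaction, baseline and one follow-up. Here λ = f²Nm/(1 − ρ), and a difference of d in change corresponds to f = d/4 = 0.1025. The total N is 312 at ρ = 0.5, 126 at 0.8, 64 at 0.9 and 58 at 0.91.
- Baseline-adjusted mean of both post-intervention measurements: 56 per arm (112 in two arms) at ρ = 0.7 and 41 per arm (82 in two arms) at 0.8. Size scales with (1 + ρ)/2 − ρ², so 29 per arm is reached only at about ρ = 0.87.

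So 58 needs a correlation of about 0.9. At ordinary correlations, figures near 58 appear only with a mis-scaled effect size:
- 0.41 entered as f in the between-groups test: 58 at ρ = 0.4 and 60 at ρ = 0.5.
- d/2 entered as the interaction f: 58 with two groups and two measurements at ρ = 0.65, and 57 with three groups and three measurements at ρ = 0.65. For a baseline-to-follow-up change this entry implies twice the stated effect, since d/2 = 2 × d/4.

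**3. Power for the primary test actually planned.** Pairwise comparison at week 8, two-sided alpha 0.0167, by noncentral t with 2n − 2 degrees of freedom and noncentrality δ√(n/2), where δ = d/√(1 − r²) after baseline adjustment. For d = 0.409, δ is 0.41, 0.47, 0.57 and 0.68 residual SD at r = 0, 0.5, 0.7 and 0.8. For example, n = 37 and r = 0 give 0.409 × √18.5 = 1.76 against a critical value of about 2.45, so power is 25%.

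| n per arm | r = 0 | r = 0.5 | r = 0.7 | r = 0.8 |
|---|---|---|---|---|
| 37 (all enrolled) | 25% | 34% | 51% | 68% |
| 29.6 = 37 × 0.8 (attrition) | 20% | 27% | 40% | 57% |
| 18.5 = 29.6/1.6 (design effect too) | 12% | 16% | 24% | 34% |

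Baseline adjustment is the favourable case; an unadjusted change score does no better (at r = 0.5 it gives the r = 0 column). With 37 per arm, 95% power needs r of about 0.90. Otherwise 95% power needs about 197, 148 or 101 per arm at r = 0, 0.5 or 0.7, before attrition and design effect.

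**4. How much is due to alpha?** At alpha 0.05, 37 per arm and no adjustment, power is 41%. The alpha mismatch makes the shortfall worse but is not its main source.

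**5. Detectable difference at alpha 0.0167, before any design effect.** With 37 per arm: 0.96 residual SD at 95% power and 0.77 at 80%. With about 30 per arm: 1.08 and 0.86.

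**The case against.** Several stronger readings are tempting, and the protocol does not support them.

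- A reader might infer that no software setting can yield 58. Step 2 shows that ordinary repeated-measures settings can, though only with a mis-scaled effect size.
- A reader might infer that d was typed in as f, or that 58 is a two-arm total wrongly spread over three arms. Neither is established. The interaction route also reaches 57 to 60, including with three groups, and the section names neither the test nor the number of groups.
- A reader might rule out a correlation of 0.9 because the questionnaire's Cronbach's alpha is 0.70. That coefficient measures internal consistency, not stability over time, and the scale has eight dimensions. A correlation that high would have to be stated and justified, but it is not disproved.
- A reader might say flatly that power is 20 to 50%, or that a true effect would more likely than not be missed. Both depend on r: at r = 0.8 power is 68%, or 57% after attrition.

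The protocol also openly says that its inputs come from a mental status examination, and its Discussion concedes that the sample size may limit power. Both are fair disclosures. Neither withdraws the 95% figure nor shows that 0.41 carries over to the primary questionnaire. Finally, the 1.6 is an allowance for cluster sampling, while participants are randomised individually, so it need not apply in full to a between-arm contrast. The third row of the table is the plan's own accounting, not a prediction.

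**Conclusion.** Wrong as written. The protocol's 95% power does not belong to its primary analysis and cannot be obtained from d = 0.41 with 58 participants unless the correlation is about 0.9, which the protocol does not state. For the planned pairwise tests at 0.0167, power with 37 per arm runs from about 25% to 68% as r goes from 0 to 0.8. It runs from about 20% to 57% after the planned attrition, and from about 12% to 34% if the full design effect also applies. These figures assume a two-sided test, a true effect of 0.41 SD on the primary questionnaire and linear baseline adjustment. Every value of r in that range leaves power well below 95%. The conflict between the two alphas needs no assumption at all.

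**What to change.** Keep the enrolment of 111 and replace the 95% power sentence. The new statement should be computed for the primary test as specified, a pairwise week-8 comparison at two-sided alpha 0.0167, and should name the assumed baseline correlation, the attrition and whether the design effect applies to the between-arm contrast. It could give the detectable differences in step 5, together with the power for d = 0.41 over a stated range of r. The target should be expressed in points of the cognitive empowerment questionnaire, using an SD for that scale, which the protocol does not now give.

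The cost is protocol wording and a less favourable stated power; no participants are added. According to Trial status, recruitment had not started at this version. Replacing the Bonferroni correction with a closed three-arm test is optional and not part of this correction. Bonferroni is valid, and the gain from a closed test is smaller when the third arm's mean lies midway between the other two.

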### Sampling method

A two-stage cluster sampling method will be used to ensure adequate sample representation. Khafr County comprises nine comprehensive health centers, including three urban and six rural centers. Additionally, the rural centers will be affiliated with 27 health posts, each responsible for providing services to local families. In the first stage, each urban and rural comprehensive health center will be considered an independent cluster. Three centers (one urban and two rural) will be randomly selected. In the second stage, sampling will be conducted from the population covered by the selected centers. In each rural center, two affiliated health posts will be randomly selected. Then, eligible participants will be randomly chosen from the registries of these health posts and the selected urban center. To maintain equal representation, 50% of participants will be selected from urban areas and 50% from rural areas.

After enrollment, participants will be assigned to one of three groups, walking, meditation, or control, using block randomization. Each block will consist of 6 individuals, with a total of 20 blocks stratified by setting: 10 urban and 10 rural. Allocation concealment will be ensured using sealed envelopes, and responsibilities will be separated so that the person enrolling participants will be different from the one assigning them to groups. Participants will be placed in blocks based on registration order. Each block’s group codes will be enclosed in a sealed envelope. Upon registration of each set of six participants, the envelope will be opened, and codes will be written on separate cards. The randomization coordinator will then be contacted to determine each participant’s group based on the assigned code. This process will be repeated for all participants. A third party using the 2022 version of the Sealed Envelope online tool, independent of both the enrolling staff and the intervention investigator, will perform randomization. To prevent information exchange between groups, the walking and meditation sessions will be scheduled at different times and supervised directly by the researcher.

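### The target of 111 allows for about 16% attrition, not the stated 20%: dividing by 0.8 gives 116 (117 for equal arms)

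*Protocol article*

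**What the plan says.** In the Protocol article, under Sample size, the base figure is given as "the minimum required sample size was determined to be 58 participants". Two adjustments follow: "To account for a possible 20% attrition rate and a design effect of 1.6 due to cluster sampling". The result is that "the final adjusted sample size was increased to 111 participants, resulting in 37 individuals per group". The section does not print the formula linking these numbers. The Abstract repeats 111.

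Under Sampling method, the allocation list is described: "Each block will consist of 6 individuals, with a total of 20 blocks stratified by setting: 10 urban and 10 rural". Allocation goes by complete sets: "Upon registration of each set of six participants, the envelope will be opened". The intended mix is that "50% of participants will be selected from urban areas and 50% from rural areas".

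**The concern.** A sample size inflated for attrition should still contain the required number after the planned loss. The plan presents 111 as doing this at 20%. If it does not, the trial misses its own minimum in exactly the situation it planned for, and a reader cannot rely on the stated allowance when judging retention later. The Discussion itself names attrition as a threat to power, so the allowance should be stated correctly.

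A smaller matter concerns the end of recruitment. Envelopes are opened per set of six, and 111 is not a multiple of six, so the last women in each setting will not form a full set.

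**Working it through.** **Inputs, all from Sample size:** base number 58 in total, design effect 1.6, attrition 20%, final target 111 (3 × 37). From Sampling method: blocks of 6, 10 blocks per setting.

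**Reproducing the plan's figure**
- Design effect: 58 × 1.6 = 92.8.
- Multiplying by 1 + 0.20: 92.8 × 1.2 = 111.36, which is the stated 111 and divides by three.
- Other routes do not give 111. Adding the two inflations gives 58 × (1 + 0.6 + 0.2) = 104.4. Applying attrition first gives 58 / 0.8 = 72.5, rounded up to 73, and 73 × 1.6 = 116.8, or 117.

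**What a 20% allowance requires**
- N × (1 − 0.20) ≥ 92.8, so N ≥ 92.8 / 0.8 = 116. The next multiple of three is 117 (39 per arm).
- Gap: 116 − 111 = 5 women, or 117 − 111 = 6 for equal arms.

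**What 111 delivers**
- Remaining after 20% loss: 111 × 0.8 = 88.8, against 92.8.
- Effective number after the design effect: 88.8 / 1.6 = 55.5, against 58.
- Attrition covered: 1 − 92.8 / 111 = 16.4%. If 92.8 is rounded up to 93, it is 1 − 93 / 111 = 16.2%.

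**Effect on power, on the plan's own premises** (95% power, alpha 0.05 taken as two-sided, normal approximation)
- The design point is 1.96 + 1.645 = 3.605 standard errors.
- With 55.5 in place of 58: 3.605 × √(55.5 / 58) − 1.96 = 1.57, which corresponds to about 94%.

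**Using the existing list**
- 20 × 6 = 120 places, 40 per arm and 60 per setting.
- After 20% loss: 120 × 0.8 = 96, above 92.8; 96 / 1.6 = 60, above 58.

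**Incomplete sets at 111**
- Split as evenly as possible, 111 is 55 + 56. Then 55 = 9 × 6 + 1 and 56 = 9 × 6 + 2.
- Eighteen full blocks give 36 per arm, with three women left over in two different blocks. They fall one per arm with probability 4/6 × 2/5 = 27%, assuming each block holds two places per arm in random order. So 37/37/37 is possible but not assured.

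**The case against.** The strongest reply is that the gap is small: five or six women and about one point of power, arising from a widely used shortcut. That stands, and it limits the weight of the point. It does not make the statement correct, because the shortcut still fails to retain the required number at the stated rate.

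It can also be said that the Data collection section keeps all randomised women in the analysis and invites those who stop sessions to give outcome data, and that Statistical methods plans imputation for up to 14% missing, which is below the 16% that 111 covers. This is only partial relief. Imputation does not restore lost information, and Study population and setting says that women who miss a session are excluded.

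A reader might go further and infer that the list of 120 places contradicts a target of 111, that an odd total breaks the equal urban–rural split, or that three women could never be allocated. The documents do not support these readings:
- Ten blocks of six is the smallest whole number that covers 55 or 56 women, so 20 blocks is what a target of 111 needs. Spare places on a list are ordinary, and nowhere does the article say 120 will be enrolled.
- A 55/56 split is rounding by one person.
- Sampling method says the allocation process is repeated for all participants, so the intent is that everyone is allocated.
- The figure of 37 per group is an overall figure. It is attainable, and nothing in the article promises it within each setting.

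**Conclusion.** The point holds for the attrition arithmetic alone. On the protocol's own inputs, 111 does not allow for 20% loss; it allows for about 16%. The target that matches 20% is 116, or 117 for equal arms. The consequence is minor: an effective 55.5 instead of 58 at 20% loss, and power of about 94% instead of 95%.

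This takes the base figure of 58 and the design effect of 1.6 as given. Correcting the inflation does not confirm that 58 is itself adequate, which is a separate question. The power figure also assumes a two-sided test and a normal approximation.

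The last incomplete set in each setting is an operational note and not an error in the sample size.

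**What to change.** Choose one of two options and state it in Sample size.

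1. **Keep 111** and restate the attrition allowance as about 16%. This costs a change of wording only. Add one sentence to Sampling method saying that women in a final incomplete set are allocated from the next block's sequence in their setting, and describe 37 per group as approximate.
2. **Keep 20%** and fill the 120 places already on the list: 40 per arm, 60 per setting, 96 remaining after 20% loss. This costs up to nine more women (120 − 111) and an update of the total in the Abstract and Sample size. All blocks are then complete, so no rule for an incomplete set is needed.

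In either case, print the formula, 58 × 1.6 / (1 − attrition), so that the target can be checked. The Trial status section says recruitment had not started at version 1.0, so under that version the correction could be made before enrolment.
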